### Adverse event reporting

Data will be collected for all serious adverse events (SAE), non-serious adverse reactions (NSAR), serious adverse reactions (SAR) and SUSAR as defined in Table 3. Adverse events (AEs), SAEs and suspected unexpected serious adverse reactions (SUSARs) will be reported in compliance with International Conference on Harmonisation (ICH)- Good Clinical Practice (GCP) Guidelines.

**Table 3 T3:** Definition of adverse events

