	**A fatal outcome**
**Definition of serious adverse reaction**	Any thrombotic event e.g. stroke, TIA
	Major Bleeding- Defined as clinically overt bleeding that is associated with:
	• A fall in haemoglobin of 2 g/dl or more, or
	• A transfusion of 2 or more units of packed red blood cells or whole blood, or
	• A critical site: intracranial, intraspinal, intraocular, pericardial, intra-articular, intramuscular with compartment syndrome, retroperitoneal, or
	• A fatal outcome
**Definition of a non serious adverse reaction**	Defined as overt bleeding not meeting the criteria for major bleeding but associated with medical intervention, unscheduled contact (visit or telephone call) with a clinician, (temporary) cessation of warfarin treatment, or associated with discomfort for the subject such as pain or impairment of activities of daily life.
	Examples of non-major clinically relevant bleeding are:
	• Epistaxis if it lasts for more than 5 minutes, if it is repetitive (i.e., 2 or more episodes of true bleeding, i.e., not spots on a handkerchief, within 24 hours), or leads to an intervention (packing, electrocautery, etc.) and no admission to hospital.
	• Gingival bleeding if it occurs spontaneously (i.e., unrelated to tooth brushing or eating), or if it lasts for more than 5 minutes
	• Haematuria if it is macroscopic, and either spontaneous or lasts for more than 24 hours after instrumentation (e.g., catheter placement or surgery) of the urogenital tract
	• Macroscopic gastrointestinal haemorrhage: at least 1 episode of melena or hematemesis, if clinically apparent
	• Rectal blood loss, if more than a few spots
	• Haemoptysis, if more than a few speckles in the sputum, or
	• Intramuscular hematoma
	• Subcutaneous hematoma if the size is larger than 25 cm^2^ or larger than 100 cm^2^ if provoked
**Definition of serious adverse event**	A serious adverse event is defined as an untoward medical occurrence in a participant of a study that does not necessarily have a causal relationship with the treatment that results in:
	• Death,
	• Is life threatening
	• Requires hospitalisation or prolongation of existing hospitalisation
	• Results in persistent or significant disability or incapacity
	• Consists of a congenital abnormality or birth defect
	Other known rare adverse reaction listed in the SmPC are:
	Skin reactions: Purpura and ecchymosis
	Pruritic lesions
	Skin necrosis
	Alopecia
	Diarrhoea
	An unexplained fall in haematocrit
	Jaundice and hepatic dysfunction

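### Table 3 uses the major/non-major bleeding grade as its seriousness class for reactions, so a clinically relevant non-major bleed that leads to admission is both non-serious and serious, and cannot be a serious adverse reaction

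*Protocol article*

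**What the plan says.** The section Adverse event reporting states that "Data will be collected for all serious adverse events (SAE), non-serious adverse reactions (NSAR), serious adverse reactions (SAR) and SUSAR", and refers to Table 3 for the definitions. Three definitions in Table 3 matter here.

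- **Serious adverse reaction.** It has two parts. One is "Any thrombotic event e.g. stroke, TIA". The other is bleeding: "Major Bleeding- Defined as clinically overt bleeding that is associated with" a haemoglobin fall of at least 2 g/dl, transfusion of at least 2 units, a listed critical site, or death. Admission is not among the criteria.
- **Non-serious adverse reaction.** "Defined as overt bleeding not meeting the criteria for major bleeding but associated with medical intervention", or with unscheduled clinician contact, an interruption of warfarin, or discomfort. A list of examples follows. The epistaxis example ends "or leads to an intervention (packing, electrocautery, etc.) and no admission to hospital". The other examples carry no such limit, for instance "Macroscopic gastrointestinal haemorrhage: at least 1 episode of melena or hematemesis, if clinically apparent".
- **Serious adverse event.** An untoward occurrence that "does not necessarily have a causal relationship with the treatment that results in" one of several consequences, among them: "Requires hospitalisation or prolongation of existing hospitalisation".

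The known rare reactions from the product label, including skin necrosis and hepatic dysfunction, are printed beneath the SAE criteria. They appear in neither reaction definition.

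Table 2 (Outcome measures) holds the same major and non-major clinically relevant bleeding definitions. There they grade the secondary outcome of bleeding events.

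**The concern.** Bleeding grade and seriousness are different scales. The grade in Table 2 describes how severe a bleed is. Seriousness depends on what happened to the patient: death, threat to life, admission, disability or congenital abnormality. Table 3 carries the grade over as if it settled seriousness. The two scales then conflict for any clinically relevant bleed that falls short of the major criteria but leads to admission.

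What is at stake is the count of serious adverse reactions. Two sites faced with the same admitted bleed could each follow a row of Table 3 faithfully and give it different labels. A site following the reaction rows strictly could never label it a serious reaction. The Background names bleeding as the concern with prolonged warfarin, so these are the reactions that safety oversight most needs classified the same way everywhere.

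**Working it through.** No arithmetic applies, and the document states no figure on this point. The check runs defined cases through the three Table 3 rows.

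| Case | Serious adverse reaction row | Non-serious adverse reaction row | SAE row |
|---|---|---|---|
| A. Gum bleed prompting an unscheduled call, no admission | Not met | Met | Not met |
| B. Bleed with haemoglobin fall of 2 g/dl, admitted | Met | Not met (it is major) | Met |
| C. Melaena, admitted, haemoglobin fall 1.5 g/dl, no transfusion, survives | Not met | Met | Met |
| D. Epistaxis, packed and admitted, no major criterion | Not met | General wording met, but the example points away | Met |
| E. Hepatic dysfunction attributed to warfarin, admitted | Not met | Not met (bleeding only) | Met |

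Cases A and B are controls. Where a minor bleed stays out of hospital, or a major bleed is admitted, the rows agree.

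Case C is the contradiction. The fall of 1.5 g/dl is below 2 g/dl, no blood was given, the site is not on the critical list, and the patient survived, so the major criteria fail. Melaena is itself a listed example in the non-serious row. Admission satisfies the SAE row. One event is non-serious and serious under the same table, and the serious adverse reaction class is closed to it however clearly warfarin caused it. The same holds for admitted haematuria, rectal bleeding, haemoptysis and haematoma, because none of those examples excludes admission.

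Case D shows that admission was considered for one type of bleed only. The restriction sits inside the epistaxis example and not in the governing definition.

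Case E is the second gap. The table itself calls the listed events reactions. However, one reaction row is confined to thrombosis and major bleeding, and the other to non-major bleeding. An admitted case can be an SAE but has no reaction class.

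Two further checks bound the consequence.

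1. **Capture.** The SAE definition does not depend on causality, and data are collected for all SAEs. Cases C, D and E are therefore recorded as SAEs. Under Thrombotic events and associated deaths, GP records are also reviewed every six months for hospital admissions, and a discharge summary is obtained.
2. **Bleeding outcome.** The secondary outcome uses the Table 2 grades. Case C counts there as non-major clinically relevant whichever seriousness label it receives.

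**The case against.** The strongest reply is that nothing is lost. An admitted bleed is an SAE whatever other row it also meets. No text says that the bleeding row overrides the SAE row. Admissions are picked up a second time through GP records, and a blinded committee decides their primary cause. The article also commits to ICH-GCP and the EU Clinical Trials Directive. Order of precedence and the procedure for judging causality could be set out in the full protocol, which is not shown.

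Most of this stands, and it rules out several stronger readings that a reader might infer:

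- *Serious warfarin bleeds go unreported.* The document does not support this, because the SAE route and the admission review both capture them.
- *The trial's harm result would be understated.* It would not be, because the bleeding outcome rests on Table 2 and not on seriousness.
- *All non-major bleeding is labelled non-serious, admission included.* This is too broad. The row requires intervention, contact, interruption of warfarin or discomfort. The epistaxis example excludes admission, and no sentence states that an admitted bleed is non-serious. The conflict arises because the definitions overlap.
- *A number of misfiled events can be given.* It cannot. The document reports neither the rate of non-major bleeding nor the share admitted, so any count would rest wholly on assumed rates.

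The reply does not remove the contradiction. Table 3 is printed in full enough to apply, and the reporting section makes it the operative definition, so this is about what the document states and not what it leaves out. Capture as an SAE does not settle whether the event is a serious *reaction*. The review of GP records finds the admission but does not say which reaction class applies.

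**Conclusion.** The point holds as a classification defect. Table 3 gives incompatible seriousness labels to a clinically relevant non-major bleed that leads to admission and bars it from the serious adverse reaction class. It also leaves admitted product-label reactions without any reaction class.

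The consequence is inconsistent classification between sites and a possible under-count of serious adverse reactions. Any under-count would probably fall mainly in Group W, on the assumption that warfarin reactions follow warfarin exposure. Its size cannot be computed from the document. SAE capture, the Table 2 bleeding outcome, the primary outcomes and the power calculation are unaffected.

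The conclusion rests on reading the Table 3 rows as printed. It assumes that no rule of precedence elsewhere in the full protocol already resolves the overlap. If there is one, the table should refer to it.

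**What to change.** Reconcile the rows of Table 3 by separating three judgements that it now merges:

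1. **Grade.** Keep major and non-major clinically relevant as the bleeding outcome grade in Table 2 only.
2. **Seriousness.** Decide it for every event by the criteria already listed in the table's SAE row.
3. **Causality.** Judge separately whether the event is related to warfarin.

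Any warfarin-related event that meets a seriousness criterion is then a serious adverse reaction. That includes an admitted non-major bleed and an admitted product-label reaction. A related event that meets none is a non-serious adverse reaction. The bleeding examples can stay in Table 2. If any remain in Table 3, the admission limit should apply to the whole definition and not to epistaxis alone.

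The cost is rewording Table 3 and the event form. A few more events will be classed and reported as serious reactions. No outcome definition, analysis or sample size changes.

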### Ethics and research governance

The trial will be conducted in compliance with the principles of the Declaration of Helsinki (1996), the principles of the ICH-GCP and run in accordance with EU Clinical Trials Directive and all of the applicable regulatory requirements. The study protocol and other documentation have been approved by Trent Research Ethics Committee and MHRA.

### Publication

The trial results will be written up for submission to a peer reviewed journal and the trial is registered with ISRCTN. No data relating to individuals will be identified in these publications.

## Discussion

This study will primarily investigate the role of extending treatment with oral anticoagulation for those patients with raised D-dimer levels prior to discontinuing treatment and will study the impact of this management on both recurrence of thrombosis and development of post-thrombotic syndrome, both extremely costly outcomes for the NHS. This strategy would allow those people who require extended anticoagulation treatment to receive it whilst ensuring that those who only require short term treatment are not exposed to unnecessary and potentially dangerous treatment.

Identifying the potential for utilisation of D-dimer POC testing will make feasible the identification of those high risk patients within a primary care setting negating the necessity for costly and inconvenient referral elsewhere. Thus people with a first unprovoked proximal DVT or PE could be managed differently to current management with the potential for significant improvements in health outcomes and patient well being.

## Abbreviations

VTE: Venous thromboembolism; DVT: Deep vein thrombosis; PE: Pulmonary embolism; PTS: Post thrombotic syndrome; NW: Randomised to Group W with normal D-dimer at point of randomisation; RW: Randomised to Group W with elevated D-dimer at point of randomisation; NRO: Randomised to Group O with elevated D-dimer at point of randomisation and then produced a normal D-dimer off treatment; RRO: Randomised to Group O with elevated D-dimer at point of randomisation and then produced an elevated D-dimer off treatment; NNO: Randomised to Group O with a normal D-dimer at point of randomisation and then produced a normal D-dimer off treatment; RNO: Randomised to Group O with normal D-dimer at point of randomisation and then produced an elevated D-dimer off treatment.

